### **3. Preliminary work done:**

Recently we conducted an open level clinical trial on HCQ as PEP for the prevention of COVID-19 in asymptomatic high risk house hold contact of the laboratory confirmed COVID-19 cases. The result was very promising showing absolute risk reduction of around 9% for prevention of COVID-19 in participant who received PEP with HCQ as compared to the control group which did not receive HCQ and there was no serious adverse event [13]. This encourages us to conduct a double blind clinical trial on HCQ as PEP for the prevention of COVID-19 in at-risk individuals. As this is an ongoing serious pandemic without any definitive therapeutic cure and preventive vaccines are still awaited this study purpose to generate adequate data at earliest, which can be utilized in reforming national and international guidelines for the battle against of COVID-19 pandemic.

### **4. Relevance clinical importance and expected outcome:**

The study will enlighten us regarding efficacy of HCQ as PEP for the prevention of COVID-19 in asymptomatic individuals who are at risk for SARS-CoV-2 infection. As a research institute of national as well as international interest, it is a great opportunity for us to produce such a robust data which can be utilized in reforming national and international guidelines for the battle against of SARS-CoV-2. As per our recently conducted open level clinical trial there was absolute risk reduction of around 9% for

prevention of COVID-19 in participant who received PEP with HCQ as compared to the control group which did not receive HCQ and there was no serious adverse event [13].

## **5. Objectives:**

**Primary objectives:** To evaluate the efficacy of Hydroxychloroquine (HCQ) as post exposure prophylaxis (PEP) for the prevention of COVID-19 in asymptomatic individuals who are at risk for SARS-CoV-2 infection.

**Secondary objectives:**

1. New onset symptoms of COVID-19
2. Compliance to the therapy
3. Difficulty faced during quarantine
4. Adverse drug reaction monitoring

## **6. Details of method:**

**Aims of the study:** To evaluate the efficacy of Hydroxychloroquine (HCQ) as post exposure prophylaxis (PEP) for the prevention of COVID-19 in asymptomatic individuals who are at risk for SARS-CoV-2 infection.

**Site of Study:** The study will be conducted in the special COVID-19 screening clinic at Emergency medical outpatient department (EMOPD) and Communicable disease ward of the Post Graduate Institute of Medical Education and Research (PGIMER), Chandigarh, India. The study will be done under the collaboration of the department of Internal Medicine, Virology, Pharmacology and Community medicine & School of public health of the institute, PGIMER, Chandigarh.

**Study Design:** It is randomized control double blind clinical trial. The study will be done in two groups. After screening of the asymptomatic individual with direct contact with laboratory confirmed COVID-19 cases will be randomized into one PEP group and one control/placebo group as per inclusion and exclusion criteria. Post exposure prophylaxis (PPE) group will receive tablet HCQ 400 mg q 12 hourly on day one followed by 400 mg once weekly for 3 weeks (total cumulative dose of 2000 mg). The control group will receive placebo instead of HCQ. Both the groups will receive standard care of therapy in the

form of home quarantine for 2 weeks along with social distancing and personal hygiene. The participants will be followed up for 4 weeks telephonically or physically as and when required.

**Study duration:** Study will be carried out during December 2020 onward to March 2021 (ongoing pandemic).

**Screening and Enrolment of Patients:** At-risk individuals presenting at COVID-19 screening clinic and through telephonic consultation will be screened for the enrollment in the study as per pre-defined inclusion and exclusion criteria. The asymptomatic individuals with high risk direct contact are family members, relatives, friends or colleagues who are living with or spend hours/days with the COVID-19 patients without taking any personal protective precautions. After screening of the asymptomatic individual with direct contact with laboratory confirmed COVID-19 cases will be randomized into one PEP group and one control/placebo group after getting informed consent.

**Inclusion and exclusion criteria:**

Irrespective of gender and age of  $\geq 18$  years, all asymptomatic individual with direct contact with laboratory confirmed COVID-19 cases will be included in the study. Individual who will not give consent for HCQ prophylaxis and patients with contraindication for HCQ therapy like, hypersensitivity to HCQ or 4-aminoquinolone derivatives, patients with known retinopathy, cardiac arrhythmia, G6PD deficiency, psoriasis and pregnancy will be excluded from the study. Also the symptomatic individual, all health care workers related to suspected or confirmed COVID-19 and who received COVID-19 vaccine will be excluded from the study.

**Method and intervention:** In this randomized control clinical trial after screening and enrolment, all the at-risk asymptomatic participants will be assigned into one PEP group and one control group as per inclusion and exclusion criteria after getting informed consent. The PEP group will receive tablet HCQ 400 mg q 12 hourly on day one followed by 400 mg once weekly for 3 weeks (total cumulative dose of 2000 mg). The control group will receive placebo instead of HCQ. Both the groups will be advised standard care of therapy in the form of home quarantine for 2 weeks along with social distancing and personal hygiene. The prophylactic dose of HCQ is decided as per ICMR recommendation for PEP with

HCQ [12]. The potential antiviral and anti-inflammatory properties of HCQ, along with the low cost, very good oral bioavailability, higher concentrations in the lungs relative to the plasma levels and acceptable safety profile supported the formulation this national advisory. After getting informed consent the drugs will be dispensed directly to the participants during the COVID-19 screening clinic visit or through door step delivery by the concerned HCW with help of the police officials. They will be followed up for 4 weeks telephonically or physically when require and will be enquire regarding development of any COVID-19 symptoms like fever, cough, sore throat, shortness of breath, diarrhea, myalgia or any adverse drug event. During follow up nasopharyngeal and or throat swab of the participants will be taken for processing reverse transcription polymerase chain reaction (RTPCR) for the detection of SARS-Cov-2 RNA to confirm the diagnosis of CoVID-19. Samples for RTPCR will be taken when any asymptomatic participants become symptomatic and by the 5-14 days of contact in asymptomatic participants through in-hospital visit at COVID-19 screening clinic at EMOPD and the institute's communicable disease ward isolation. Only the participant with RTPCR positive for SARS-CoV-2 and with or without symptoms will be defined as definite COVID-19 case. The participant with new onset symptoms, but RTPCR negative for SARS-CoV-2 or cannot be performed for any reason will be defined as probable COVID-19 case. Both the definite and probable COVID-19 cases together are defined as COVID-19 case. Asymptomatic participants with negative RTPCR will be defined as non-COVID case. Incidence of COVID-19, definite COVID-19 and probable COVID-19 in previously asymptomatic participants will be compared between the PEP and control groups. Baseline routine investigations (blood, CXR, ECG) at upfront may not be possible as each participant will be the potential source of SARS-CoV-2 and additional contact with HCW will spread the virus to the healthy individual. ECG will be offered to each participant at baseline and at the end of the study. Participants will be interviewed during the follow up for any adverse events and ECG will be repeated as per indication. During follow up if any individuals become symptomatic then all relevant investigations will be done as per indications. The participants, who turned out to be definite COVID-19, were shifted to the Nehru Hospital Extension (NHE), a dedicated COVID-19 centre, of the institute PGIMER, Chandigarh and managed as per institutional COVID-19 protocol. Participant

with Probable COVID-19 were advised to continue with home quarantine. The participants with new onset COVID-19 will be managed as per institute's COVID-19 management protocol and the participants needing admission will be given best possible medical care in the institute's SARI/Nehru extension COVID ward under isolation.

**Primary outcome:** Incidence of COVID-19, definite COVID-19 & probable COVID-19

**Secondary outcome:** 1. New onset symptoms of COVID-19, 2. Compliance to the advised therapy, 3. Number of difficulty faced during quarantine, 3. Incidence of adverse drug reaction

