Presently many scientist and doctors are recommending many existing available drugs (Ribavirin, lopinavir, Remdesivir, chloroquine, hydroxychloroquine) for SARS-CoV-2 infection for therapeutic and as well as prophylactic purpose [5,6]. Among which hydroxychloroquine sulphate (HCQ), a chloroquine analogue has given some rays of hope to battle against this deadly pandemic [7]. In vitro studies showed that HCQ had potent anti viral effect against SARS-CoV through mechanism targeted at the host cell [8-10]. HCQ is quite safe drugs as it is being used in rheumatology patients for lifelong therapy without much side effect, so it allow for higher dose without any significant side effects and drug-drug interaction [11]. Recently published clinical trial suggested HCQ can be used for the therapeutic purpose of the SARS-CoV-2 infection [7]. ICMR has advised for HCQ prophylaxis for the people who are at risk for developing SARS-CoV-2 infection, all asymptomatic health care workers involved in taking care of suspected or confirmed COVID-19 cases and all asymptomatic household contacts of laboratory confirmed COVID-19 cases [12]. This encouraged us to conduct an open level clinical trial on HCQ as PEP for the prevention of COVID-19 in asymptomatic high risk house hold contact of the laboratory confirmed COVID-19 cases. The result was very promising showing absolute risk reduction of around 9% for prevention of COVID-19 in participant who received PEP with HCQ as compared to the control group which did not receive HCQ and there was no serious adverse event [13]. But there is still conflicting scientific data to prove or disprove the efficacy of HCQ for the treatment and post exposure chemo-prophylaxis for SARS-CoV-2 infection management. Recently published study proposed that HCQ was not useful as post exposure prophylaxis (PEP) for prevention of COVID-19 in at risk individual [14]. But in this study majority of the participants were health care workers (HCW). Recently newer studies have come in support of HCQ for the potential preventive measure against COVID-19 [13, 15].

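### Eligibility does not exclude people already taking HCQ or chloroquine and follow-up does not ask about it, although the protocol says HCQ is nationally advised for household contacts, so the placebo contrast could be diluted unmeasured

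*Protocol*

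**What the plan says.** **Who gets in.** Under Inclusion and exclusion criteria (section 6), adults qualify on one condition: "all asymptomatic individual with direct contact with laboratory confirmed COVID-19 cases will be included in the study". Screening and Enrolment of Patients describes high-risk contacts as "family members, relatives, friends or colleagues who are living with or spend hours/days with the COVID-19 patients".

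**Who is kept out.** People who refuse consent and people with contraindications to HCQ are excluded. After hypersensitivity, the text says that "patients with known retinopathy, cardiac arrhythmia, G6PD deficiency, psoriasis and pregnancy will be excluded from the study". Symptomatic people are also excluded, and "all health care workers related to suspected or confirmed COVID-19 and who received COVID-19 vaccine will be excluded from the study". The Project summary gives the same list. Neither place mentions present or past use of HCQ or chloroquine.

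**What contacts are advised to take.** Section 2 states that "ICMR has advised for HCQ prophylaxis for the people who are at risk for developing SARS-CoV-2 infection" and names among them "all asymptomatic household contacts of laboratory confirmed COVID-19 cases [12". The Project summary and section 1 say the same. The trial regimen comes from that source: "The prophylactic dose of HCQ is decided as per ICMR recommendation for PEP with" HCQ.

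**What both arms receive, and what is asked.** Study Design and Method and intervention describe standard care as home quarantine, distancing and hygiene. Participants are followed for 4 weeks and asked about COVID-19 symptoms and adverse drug events. The compliance outcome concerns the advised therapy. Non-study HCQ is not mentioned.

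**The concern.** A placebo-controlled trial of a drug that its own population is being advised to take needs a rule for people who already take it. Here a household contact who has begun the advised prophylaxis meets every written criterion and can be allocated to placebo. So can a contact taking HCQ for another reason; section 2 notes that "it is being used in rheumatology patients for lifelong therapy without much side effect".

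The sample size assumes a control arm free of the drug. The 20% control rate is taken from an institutional pilot (19.5% against 10.6%), whose control group sections 2 and 3 describe as not having had HCQ. The new protocol borrows that rate without writing in the condition behind it. It does exclude vaccinated people, a competing preventive measure, but not users of the test drug.

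At stake are some loss of power and the reading of a null result. If nobody asks about non-study use, its extent cannot be established afterwards.

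**Working it through.** **Inputs.** From Sample size & statistical analysis: 20% control, 10% PEP, 200 per arm, 80% power, one-sided 0.05. The fraction *c* of placebo participants taking HCQ is not in the documents, so 10, 20 and 30% are assumptions.

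**Step 1: reproduce the planned size.** Pooled-variance formula, no continuity correction, with p̄ the mean of the two rates:

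n per arm = [z_α √(2p̄(1−p̄)) + z_β √(p₁(1−p₁) + p₂(1−p₂))]² / (p₁−p₂)²

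For 0.20 and 0.10: p̄ = 0.15, √(2 × 0.15 × 0.85) = 0.505, √(0.16 + 0.09) = 0.5.

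- Two-sided 0.05: (1.960 × 0.505 + 0.842 × 0.5)² / 0.01, which rounds up to 199 per arm, 398 in total. This reproduces the planned 400.
- One-sided 0.05: (1.645 × 0.505 + 0.842 × 0.5)² / 0.01, which rounds up to 157 per arm, 314 in total (354 with continuity correction). This does not reproduce 400.

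The stated level and the stated size therefore do not correspond, and both levels are shown below.

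**Step 2: dilution model.** Each placebo participant taking HCQ is given the PEP-arm risk:

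control risk = 0.20(1−c) + 0.10c = 0.20 − 0.10c

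The PEP-arm risk stays at 0.10. For a given *c* this is an upper bound on dilution, provided non-study HCQ protects no better than the study course.

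**Step 3: power at 200 per arm.**

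power = Φ{ [(p₁−p₂)√n − z_α √(2p̄(1−p̄))] / √(p₁(1−p₁) + p₂(1−p₂)) }

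Check at c = 0, two-sided: (0.10 × 14.142 − 1.960 × 0.505) / 0.5 = 0.849, and Φ(0.849) = 80.2%.

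| Assumed use *c* | Control risk | Difference | RR | Power, one-sided 0.05 | Power, two-sided 0.05 | Total N for 80%, one-sided / two-sided |
|---|---|---|---|---|---|---|
| 0 | 20% | 10 points | 0.50 | 87.8% | 80.2% | 314 / 398 |
| 10% | 19% | 9 points | 0.53 | 82.1% | 72.6% | 378 / 480 |
| 20% | 18% | 8 points | 0.56 | 74.7% | 63.6% | 464 / 590 |
| 30% | 17% | 7 points | 0.59 | 65.8% | 53.5% | 588 / 746 |

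**Step 4: could existing text close the gap?** The exclusion for contraindications is open-ended, but a person tolerating HCQ is not contraindicated. The consent exclusion concerns refusal of prophylaxis, not prior use. Giving the control arm placebo describes the study drug and does not screen anyone out. Excluding health care workers removes one group named in the advisory but leaves household contacts.

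**The case against.** The strongest reply is that contamination is hypothetical. An advisory is not evidence of uptake, and no section reports a contact taking HCQ outside the study. The advisory covers household contacts, whereas the trial also enrols friends and colleagues. The rheumatology remark is made about safety; it says nothing about how many contacts use the drug or how often. The pilot, run by the same team in household contacts, describes its controls as untreated with HCQ. All of this stands: the size is unknown and may be small. It does not supply the missing criterion or question.

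Second, the pilot's eligibility rules are not visible. If some pilot controls did take HCQ, part of the dilution is already in the 20%. That cannot be settled from the documents.

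Third, at the one-sided level as written, 10% use still leaves power above 80%. That is correct.

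Fourth, the study design figure and some pages were not available for this check and might address HCQ use. The point is therefore limited to the eligibility and follow-up text that can be read. Leaving the matter to an analysis plan is no answer, because eligibility belongs in the protocol.

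A reader might also infer a safety breach, since study drug on top of a participant's own HCQ would exceed the 2000 mg total in Ethical justification. The documents do not support this: that section also relies on the safety of prolonged use, and section 2 says higher doses are tolerated.

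**Conclusion.** The point holds as a gap in the written eligibility and follow-up text. Users of the test drug can enter the placebo arm, and the described follow-up would not detect them. It should be corrected.

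The consequence is conditional on HCQ having the assumed effect and on placebo-arm use being appreciable. Under the upper-bound model, 10% use costs about 6 points of power one-sided (87.8 to 82.1%) or about 8 two-sided (80.2 to 72.6%). At 20% use, power is below 80% at either level.

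Two stronger readings are not supported. A reader might infer that the placebo arm was contaminated, or that this explains the similar incidences in eTable 1 (4.1% and 4.0%); no document reports any non-study use. A reader might also infer that a null result could not count against HCQ at all. With an unknown and possibly small fraction, that is too absolute: the relative risk moves only from 0.50 to 0.53 at 10% use. What is lost is the ability to show that dilution was small.

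**What to change.** - Add current or recent HCQ or chloroquine use, for any reason, to the exclusions in both the Project summary and Inclusion and exclusion criteria. The sponsor should set and justify the look-back window; the documents offer no basis for a figure.
- Ask about non-study HCQ or chloroquine at screening and at each follow-up contact, and record the answer.
- Keep every participant in the randomised arm for analysis, and report non-study use by arm.
- Reconcile the national advisory cited in the Project summary and sections 1 and 2 with the standard care described for both arms in Study Design and Method and intervention. Whether non-study HCQ is permitted during follow-up is for the sponsor to decide and state.

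The cost is one criterion, one screening question and one follow-up question. The downside is losing a few contacts already on HCQ, who add little to the contrast.

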
with contraindication for HCQ therapy like, hypersensitivity to HCQ or 4-aminoquinolone derivatives, patients with known retinopathy, cardiac arrhythmia, G6PD deficiency, psoriasis and pregnancy will be excluded from the study. All symptomatic individual and all health care workers related to suspected or proven COVID-19 and who received CoVID-19 vaccine will be excluded from the study. The PEP group will receive tablet HCQ 400 mg q 12 hourly on day one followed by 400 mg once weekly for 3 weeks (total cumulative dose of 2000 mg). The control group will receive placebo instead of HCQ. Both the groups will receive standard care of therapy in the form of home quarantine for 2 weeks along with social distancing and personal hygiene. They will be followed up for 4 weeks telephonically or physically as and when required and will be enquired regarding development of any COVID-19 symptoms like fever, cough, sore throat, shortness of breath, diarrhoea, myalgia. During follow up nasopharyngeal swab of the participants will be taken for processing reverse transcription polymerase chain reaction (RTPCR) for the detection of SARS-CoV-2 RNA to confirm the CoVID-19. Samples for RTPCR will be taken when any asymptomatic participants becomes symptomatic and by the 5-14 days of contact in asymptomatic participants through in-hospital visit at the institute's COVID-19 screening clinic at Emergency medical out patients department (EMOPD) or communicable disease ward isolation. The participants with new onset COVID-19 will be managed as per institute's COVID-19 management protocol and the participants needing admission will be given best possible medical care in the institute's SARI/Nehru extension COVID ward under isolation. Only the participant with RTPCR positive for SARS-CoV-2 and with or without symptoms will be defined as definite COVID-19 case. The participant with new onset symptoms, but RTPCR negative for SARS-CoV-2 or cannot be performed for any reason will be defined as probable COVID-19 case. Asymptomatic participants with negative RTPCR will be defined as non-COVID case. The incidence of COVID-19 will be compared between the PEP and control groups. Department of internal medicine (Emergency) will be taking care of screening, enrolment, patients management, follow up and data analysis. Department of pharmacology will take care of randomization & blinding and adverse events monitoring. Department of Virology will take care of molecular diagnosis of COVID-19 by RTPCR as and when required. Department of Community medicine & school of public health will take care of contact tracing and information to the local IDSP.

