### **2. Background and rational of the study:**

Novel corona virus (SARS-CoV-2) epidemic which started from Wuhan in China is now a well established pandemic affecting more than 57 million people worldwide with more than 1.3 million of mortality [1]. After Italy, Spain, Germany, United Kingdom and Brazil have taken over from China in term of the burden of mortality, India is the next epicentre of this pandemic just behind USA. COVID-19 affected more than 9 million of people with more than 130 thousand of death in India [2]. The clinical presentation of the COVID-19 varies from asymptomatic cases and mild symptoms of fever, cough, sore throat, headache, myalgia, nasal congestion, diarrhea to severe pneumonia, acute respiratory distress syndrome (ARDS) requiring mechanical ventilation and even multi-organ dysfunction syndrome (MODS), sepsis leading to death [3]. If adequate preventive and therapeutic measures are not taken, India has very high risk of affecting million of people with high mortality because of the large population, very

high population density and ongoing relaxation of the previously imposed lockdown. At present there are no definitive therapeutic drugs or vaccine available for the treatment and prevention of SARS-CoV-2 infection. Symptomatic and supportive care are being given to COVID-19 cases along with isolation and quarantine measure are being taken for the suspected individual at risk for COVID-19 to limit the spread of the SARS-CoV-2 infection [4].

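### Contacts with a known earlier COVID-19 infection can be enrolled, and a residual positive swab would count as a new definite case (minor)

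*Protocol*

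**What the plan says.** **Who enters.** Under Inclusion and exclusion criteria, for adults, "all asymptomatic individual with direct contact with laboratory confirmed COVID-19 cases will be included in the study". Besides refusal of consent and contraindications to HCQ, the exclusions cover people with symptoms and staff who deal with COVID-19 patients, and the text adds that anyone "who received COVID-19 vaccine will be excluded from the study". The project summary (section 7) carries the same list, ending with those "who received CoVID-19 vaccine will be excluded from the study". Past SARS-CoV-2 infection appears in neither place.

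**What counts as an event.** Under Method and intervention: "Only the participant with RTPCR positive for SARS-CoV-2 and with or without symptoms will be defined as definite COVID-19 case". Definite and probable cases together form the COVID-19 outcome, and all three incidences are listed as primary.

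**When swabs are taken.** At onset of symptoms, or "by the 5-14 days of contact in asymptomatic participants". No RT-PCR or serology before randomisation is described. On other entry tests the protocol says: "Baseline routine investigations (blood, CXR, ECG) at upfront may not be possible".

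**Background.** Section 2 says: "COVID-19 affected more than 9 million of people with more than 130 thousand of death in India [2]". Enrolment is planned from December 2020 to March 2021.

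**The concern.** The trial asks whether HCQ prevents COVID-19 after an exposure. A contact who has recovered from an earlier confirmed infection may be less likely to have a new one. If that person still carries viral RNA at the asymptomatic swab, the case definition records a new definite case that prophylaxis could not have prevented. Nothing in the definition separates the two situations: it asks neither for a negative swab at entry nor for the absence of an earlier positive test. The outcome text does refer to participants who were previously asymptomatic, but that describes symptoms, and a recovered contact can be asymptomatic at entry.

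This is separate from infection already incubating at randomisation, which a history cannot reveal. A past confirmed episode can be found by asking. At stake are some loss of power and, through residual positives, an RR drawn towards 1.

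**Working it through.** **1. Reproduce the planned size.** Inputs from Sample size & statistical analysis: 20% vs 10%, 80% power, level 0.05, 200 per group. With p̄ = (p₁ + p₂)/2,

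n per arm = [z_α √(2p̄(1−p̄)) + z_β √(p₁(1−p₁) + p₂(1−p₂))]² / (p₁−p₂)².

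Two-sided 0.05 gives 199 per arm, which matches the stated 200. One-sided 0.05, as the section labels it, gives 157. The two-sided basis is used below because it reproduces the plan's number.

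**2. Power with nobody affected.** Power = Φ{[(p₁−p₂) − 1.96·SE₀]/SE₁}, where
- SE₀ = √(2 × 0.15 × 0.85/200) = 0.0357
- SE₁ = √((0.16 + 0.09)/200) = 0.0354

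(0.10 − 0.0700)/0.0354 = 0.849, so power is 80.2%.

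**3. Model for past infection.** Let q be the share of participants with a known confirmed past infection and s the share of these with a residual positive swab. Assume they have no new infections and that everyone else keeps the planned rates:

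p₁ = 0.20(1−q) + qs, p₂ = 0.10(1−q) + qs.

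With s = 0, both rates shrink by the same factor and the RR stays at 0.50. Only s > 0 moves it.

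**4. Values for q and s.** The documents give neither. The one figure bearing on q is the count of more than 9 million cases in India. With an assumed population of 1.3-1.4 billion (not in the documents), 9/1,400 to 9/1,300 is 0.64-0.69%, or about 0.7%. Local or household prevalence could be higher, so q is taken up to 5%. The range 0-10% for s is an assumption.

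**5. Results (200 per arm, two-sided 0.05).**

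| q | s | p₁ | p₂ | RR | Power |
|---|---|---|---|---|---|
| 0 | – | 20.00% | 10.00% | 0.500 | 80.2% |
| 0.7% | 0 | 19.86% | 9.93% | 0.500 | 79.9% |
| 0.7% | 10% | 19.93% | 10.00% | 0.502 | 79.7% |
| 2% | 0 | 19.60% | 9.80% | 0.500 | 79.3% |
| 2% | 10% | 19.80% | 10.00% | 0.505 | 78.8% |
| 5% | 0 | 19.00% | 9.50% | 0.500 | 77.8% |
| 5% | 10% | 19.50% | 10.00% | 0.513 | 76.6% |

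**6. False cases per arm.** These number 200·q·s: 200 × 0.007 × 0.10 = 0.14 at the low end and 200 × 0.05 × 0.10 = 1 at the high end.

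**The case against.** The strongest objection is about size. A reader might infer that a large share of contacts, say 10-20%, had recovered. The same formula then gives power of 75.2% (q = 10%, s = 0) down to 63.6% (q = 20%, s = 10%). The documents do not support such shares for laboratory-confirmed infection. Most of that group would be undiagnosed, and a history question would not remove them. The loss at those shares is therefore not one that this fix prevents. This objection stands, and it is why the range above stops at 5%.

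Four further points:

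- **Possible double counting.** The 20% and 10% rest on the institution's own pilot (19.5% vs 10.6%). Nothing in the protocol says that the pilot excluded past infection. If it did not, those rates already include some recovered people, and the calculation overstates the loss. This stands as a reason to read the table as an upper estimate for each q and s.
- **Level of the test.** At the one-sided 0.05 that the protocol states, 200 per arm gives 87.8% power, and q = 5% with s = 10% leaves 85.2%. This stands, but the mechanism is the same on either basis.
- **No stated contradiction.** A reader might infer from the vaccine exclusion that the sponsor requires susceptible participants and has contradicted itself. The protocol gives no reason for that exclusion, so a contradiction cannot be shown. Enrolling contacts by exposure regardless of history is a defensible choice. The gap in the case definition remains.
- **No bias towards one arm.** With randomisation and blinding, past infection should fall equally on both groups in expectation. This stands: the harm is dilution only.

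**Conclusion.** The point holds as a minor one. As written, the protocol permits enrolment of contacts with known earlier COVID-19 and would count a residual positive swab from that infection as a new primary event. It does not show that such people are enrolled in any number.

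Under the stated assumptions power drops by between 0.3 and 3.6 percentage points, and the RR moves from 0.50 by no more than about 0.013. The upper end needs a confirmed share about seven times the assumed national one, with one in ten of those people still positive. The estimate also assumes that recovered participants have no new infections and that the pilot-based rates do not already include them. The reason to act is that the gap is cheap to close, not that it threatens the trial's conclusion.

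**What to change.** Add to the exclusion list, beside the vaccine criterion: previous laboratory-confirmed COVID-19 (by history at screening). Make the same change in the project summary (section 7) and under Inclusion and exclusion criteria, so that the two lists stay identical.

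The cost is one screening question, with no added test, and the loss of a few recruits. The result would then apply to people without known prior infection. Undiagnosed past infection would remain, so the change reduces the problem without removing it.
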